## Rationale

PMS entails clinically significant somatic and psychological symptoms in the premenstrual phase of the menstrual cycle, causing substantial distress and functional impairment.^10^ Worldwide, a considerable amount of women of reproductive age are affected with a pooled prevalence of 47.8%.^11^ Subsequently, a myriad of distinctive therapies are prescribed for PMS—including pharmacological and phytopharmaceutic drugs as well as complementary interventions^12^—yet there is limited evidence for some interventions (eg, Chaste tree; anxiolytics) while other empirically validated interventions (eg, selective serotonin reuptake inhibitors, hormonal therapy) show considerable side-effects.^13^

Notably, PMS seems to be highly susceptible to placebo effects: The Royal College of Obstetricians and Gynaecologists alerts to substantial placebo responses in randomised-controlled PMS intervention trials of 36%–43%^7^ and different studies reported considerable placebo effects on PMS.^8 9 14^ Furthermore, PMS offers the opportunity to investigate OLP effects on *both* somatic and psychological symptoms since symptom diaries like the German PMS symptom diary inquire about physical (eg, breast tenderness, headaches, joint and muscle pain) as well as psychological symptoms (eg, depressed mood, hopelessness, irritability). In addition, we are the first to assess the effect of a comprehensive OLP treatment rationale in a clinical population. We hypothesise that first, women obtaining an OLP treatment with a treatment rationale will report less PMS symptom intensity and interference during the course of the intervention and at follow-up, compared to women obtaining an OLP treatment without a treatment rationale. Second, we assume that women receiving an OLP treatment without a treatment rationale will also show a higher decrease in PMS symptom intensity and interference in comparison to the treatment as usual (TAU) group which is not given any of the treatment-specific information that the OLP groups receive nor the rationale for the OLP treatment.

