## Objectives

### Primary objectives

The primary objective of this study is to test the effectiveness of an OLP treatment in women suffering from moderate to severe PMS in regard to PMS symptom intensity and interference. Also, we examine whether there is a group difference across time. Moreover, we test whether a comprehensive OLP treatment rationale has an effect on the OLP response compared to omitting the treatment rationale.

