### Statistical analysis

For the testing of the primary hypotheses, the daily data from three menstrual cycles of a symptom diary is examined. Because of the hierarchical structure of the data (menstrual cycles as level-1 are nested within participants as level-2) and given our aim to predict post-interventional changes between menstrual cycles as the primary outcome, a multilevel modelling approach will be adopted. Multilevel models take care of the interdependence of the hierarchical data that arises due to the fact that observations within the same individual are typically more similar to each other compared to observations between individuals.^30 31^ Here, we will analyse temporal changes across menstrual cycles of symptom intensity and interference among the different study groups. To compare a TAU group with two intervention groups and to evaluate the effect of the applied treatment rationale, the following linear a priori contrast will be tested for the factor study group: TAU<OLP−<OLP+. Thus, based on published findings,^6^ we expect that the effect of OLP− lies between that of TAU and OLP+. Out statistical model contains menstrual cycle as within-subject factor with three levels (C1, C2 and C3), study group as between-subject factor with three levels (TAU, OLP+ and OLP–), and the interaction between the two factors. In line with recommendations by Fitzmaurice *et al*,^32^ we will treat baseline values (ie, values at C1) as a part of the outcome vector and assume that the means among study groups are equal at baseline since participants are randomised. The model contains the two main effects study group contrast (defined above) and menstrual cycle (temporal effect) plus the interaction between the two. We will be primarily interested in the interaction term as it tests for the differential temporal change between study groups in order as defined in the linear contrast.

Analyses of secondary outcomes are based on the same multilevel model as used for primary outcomes, but will be considered exploratively, thereby not correcting for multiple tests.^33^

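### The primary linear contrast, read with the usual weights and three equal arms, tests only OLP+ against TAU and so tests neither of the two stated hypotheses nor the rationale question

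*Protocol article*

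**What the plan says.** The Rationale section sets two directional hypotheses. The first is that women given OLP with a rationale will have less symptom intensity and interference "compared to women obtaining an OLP treatment without a treatment rationale". The second is that OLP− women "will also show a higher decrease in PMS symptom intensity and interference in comparison to the treatment as usual (TAU) group". Primary objectives repeats the first as a question: "we test whether a comprehensive OLP treatment rationale has an effect on the OLP response compared to omitting the treatment rationale". The second research question in Box 1 asks the same.

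The Statistical analysis section gives one tool for both jobs. The purpose is "To compare a TAU group with two intervention groups and to evaluate the effect of the applied treatment rationale", and for this "the following linear a priori contrast will be tested for the factor study group: TAU<OLP−<OLP" (the last arm is OLP+). On which term decides, it gives main interest to the interaction of this contrast with cycle, because that term "tests for the differential temporal change between study groups in order as defined in the linear contrast".

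The group term is described twice. One sentence has study group as a between-subject factor with three levels, crossed with cycle. A later one says: "The model contains the two main effects study group contrast (defined above) and menstrual cycle (temporal effect) plus the interaction between the two". No OLP+ versus OLP− or OLP− versus TAU contrast is named.

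**The concern.** Both hypotheses are statements about OLP−: one compares it with OLP+, the other with TAU. The Discussion says that this arm was added to test the effect of the rationale. A linear trend over three equally spaced levels gives the middle level zero weight, so the arm on which both hypotheses turn does not enter the estimate.

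At stake is the answer to a primary question. The same significant contrast would arise if the rationale added nothing to the pills, if pills without a rationale did nothing, or if OLP− did worse than TAU. Conversely, a real benefit of OLP− over TAU would be missed if OLP+ happened to be no better than TAU. The text says that the contrast evaluates the rationale, and it does not.

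**Working it through.** **Inputs from the protocol article.** 50 per arm, alpha 0.05, medium effect f = 0.25 or d = 0.5, correlation 0.5 between cycles (all from Sample size); three cycles C1 to C3 with C1 as baseline (Statistical analysis).

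**Assumptions.** Weights −1, 0, +1; a two-sided test; outcome SD of 1 in each cycle; the same benefit in C2 and C3; and the position of OLP−, shown as a range.

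**The plan's own figures.** For the analysis of covariance I used a noncentral F with 2 numerator df, N − 4 denominator df and λ = f²N. This gives N = 158 at power 0.8 and 206 at 0.9. For the repeated-measures analysis, λ = f²N × 3/(1 − 0.5) for interaction and cycle, and λ = f²N × 3/(1 + 2 × 0.5) for group. This gives 36, 30 and 108. All five figures reproduce. All are omnibus F tests; none is sized for the linear contrast or for a pair of arms.

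**What the contrast estimates.** The least-squares slope on scores −1, 0, +1 with 50 per arm puts weights −0.5, 0, +0.5 on the TAU, OLP− and OLP+ means. The estimate is (OLP+ − TAU)/2, and its test is the test of OLP+ against TAU. With unequal arms the weight on OLP− is small: +0.02 for 45/50/40 and −0.04 for 40/50/50 (TAU/OLP−/OLP+).

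**Power.** Take the mean of C2 and C3, adjusted for C1.
- Variance of the mean: (1 + 0.5)/2 = 0.75. Its covariance with C1 is 0.5, so the residual variance is 0.75 − 0.5² = 0.50.
- Standard error of a difference between two arms: √(0.50 × 2/50) = 0.1414.
- Difference of 0.5 SD: noncentrality 0.5/0.1414 = 3.54, power 0.94.
- Difference of 0.25 SD: noncentrality 1.77, power 0.42.
- Difference of 0.2 SD: noncentrality 1.41, rejection rate 0.29.

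Two-sided rejection rates, with benefit in SD for (TAU, OLP−, OLP+):

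| True benefit | Linear contrast | OLP− vs TAU | OLP+ vs OLP− |
|---|---|---|---|
| (0, 0.5, 0.5): rationale adds nothing | 94% | 94% | 5% |
| (0, 0, 0.5): pills alone do nothing | 94% | 5% | 94% |
| (0, −0.2, 0.5): OLP− worse than TAU | 94% | 29%, wrong direction | >99% |
| (0, 0.25, 0.5): OLP− midway | 94% | 42% | 42% |
| (0, 0.5, 0): benefit only in OLP− | 5% | 94% | 94%, wrong direction |

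In the midway case both adjacent tests succeed together only about 10% of the time.

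A simulation of 4,000 trials per scenario, fitting the linear score as the only group term, gave 93%, 94% and 94% for OLP− at 0.5, 0 and 0.25. At −0.3 it gave 92%; the small drop arises because the lack of fit goes into the residual variance.

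On a single standardised score without the gain from averaging and baseline adjustment, the standard error is √(2/50) = 0.20. The contrast then has 70% power wherever OLP− lies, and each adjacent pair has 24% in the midway case. The level depends on the model; the indifference to OLP− does not.

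**The case against.** **The model also has a three-level factor.** This stands. If the full factor is fitted, the OLP− mean is free and both adjacent differences can be estimated. A reader might infer from the contrast-only sentence that the plan forces OLP− to the midpoint and reports one common step for pill and rationale. That holds only under the contrast-only reading, and the text supports both. The zero weight in the primary test holds under either.

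**The contrast answers something that matters.** This stands too. OLP+ versus TAU speaks to the effectiveness objective in Primary objectives and to the first question in Box 1. It would go too far to say that the primary analysis misses every primary question; the gap is the two hypotheses in Rationale and the question about the rationale.

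**An article may leave follow-up contrasts to the full plan.** This would answer a complaint that pairwise tests are missing. It does not answer what the article says positively, namely that this contrast evaluates the rationale.

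**The harm is predicted.** The article does not say that a significant contrast will be taken to confirm each step. Still, it offers no other primary test for those steps.

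**The power figures are not for the planned test.** They use the C2/C3 mean, whereas a three-level cycle factor gives the contrast-by-cycle interaction 2 df. The percentages are therefore indicative. The weight on OLP− is the same in either form.

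**Conclusion.** The concern holds in this form. With the usual weights and equal arms, the primary contrast is a test of OLP+ against TAU. It serves the effectiveness question for OLP with a rationale, but neither adjacent hypothesis and not the rationale question that the text assigns to it. At 50 per arm, correlation 0.5 and OLP+ minus TAU of 0.5 SD, it is significant about 94% of the time wherever OLP− lies, while each adjacent pair has about 42% power if OLP− is midway.

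The conclusion rests on weights that the article does not print and on near-equal arms; modest imbalance changes little. The percentages rest further on the C2/C3 average, two-sided testing and assumed positions of OLP−. Whether the fitted model would constrain OLP− to the midpoint cannot be settled from the text, which describes the group term in two ways.

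**What to change.** 1. State once that study group is a full three-level factor crossed with cycle, under the equal-baseline constraint already planned, and remove the contrast-only description.
2. Name the group-by-cycle contrasts OLP+ versus OLP− and OLP− versus TAU as the tests of the two hypotheses, with OLP+ versus TAU for the overall effect.
3. Require the global group-by-cycle test first: 4 df, or 2 df if a single change to the average of C2 and C3 is prespecified. Then test the pairs at the same level. With three arms this is a closed procedure within one outcome. Do not use the linear contrast as the gate: in the (0, 0.5, 0) case it passes only 5% of the time and would block a true OLP− effect.
4. State how alpha is handled across the two primary outcomes, intensity and interference; the closed procedure covers one outcome only.
5. Keep the linear contrast as supportive evidence of trend, print its weights, and say that it does not establish either adjacent step.

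**Cost.** Analysis wording only; arms, visits and data stay as they are. The price is that the lower power of the adjacent comparisons becomes visible and should be reported. By normal approximation on a single score, 80% power needs 63 per arm for a difference of 0.5 SD and 252 for 0.25 SD. With the residual variance halved as above, the latter becomes 252 × 0.5 = 126 per arm, against the 50 planned.

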### Monitoring

The study is monitored for quality and regulatory adherence. The monitor, who is not involved in our study and approved by the local ethical committee, verifies the qualification of the investigators and study team members, and monitors sound and appropriate documentation.

### Ethics and dissemination

The present protocol and applied informed consent forms were approved with regard to their content and compliance with ethical regulations by the Ethics Committee Northwest and Central Switzerland. The study is carried out with principles enunciated in the current version of the Declaration of Helsinki^34^ and the guidelines of Good Clinical Practice issued by the International Conference on Harmonization.^35^

Women interested in study participation receive a participant information sheet and consent form, describing the study and providing sufficient information for an informed decision about participation and data confidentiality and detailed oral information is provided. The results of the planned analyses will be published in a peer-reviewed journal.

## Discussion

Given the huge burden of women suffering from PMS,^11 36^ it is necessary to optimise treatment options and to enhance the understanding of intra-interventional processes in PMS treatment. Moreover, interventions - including medical or psychotherapeutic treatment - can generally benefit from an increased comprehension of treatment context-factors and related meaning responses^37 38^ involved in ailment amelioration. We therefore address the investigation of PMS-interventional context-factors and OLP effects and mechanisms with our study and strive to contribute to further knowledge in both areas. Previous randomised controlled trials of PMS interventions indicate high placebo responses.^7^ The presented trial is essential to test whether an OLP response can also be elicited in PMS and whether an amelioration of symptoms occurs primarily on a somatic or psychological level. Additionally, we assess the importance of a comprehensive treatment rationale in a clinical population independent of a specific intervention.

So far, there have been different aspects of previous OLP studies which have been critically evaluated in a meta-analysis of clinical OLP studies.^39^ For instance, a lack of an adequate control group in OLP trials has been pointed out. To address this issue, the TAU control group of our trial has the same amount of contact with the study staff as the two intervention groups. Furthermore, we added an OLP− group to test the effect of a comprehensive OLP treatment rationale in a clinical population. Hence, we aim to assess whether placebo pills alone are sufficient or whether a comprehensive treatment rationale is vital to elicit an OLP response and, thus, strive to distinguish OLP effects from positive framing.^39^

Moreover, to tackle previous critique of potential researcher bias and lack of blinding,^39^ any interactions with participants regarding the study proceedings, including data collection, are conducted by study team members who do not provide the intervention and who are not informed about study group allocation at the study visit. The intervention is provided by one person only ([name]) who is not involved in any interactions related to data collection. Furthermore, we decided to not provide the treatment rationale to all participants, primarily to test the effect of the treatment rationale and to avoid any experiences of disappointment in the TAU control group. A further advantage of our study is the large planned sample of 150 participants, tackling a further previously mentioned critique point.^39^

Because we are interested in understanding mechanisms of OLP responses, we assess an array of different questionnaires including attitudes and experiences of participation in the different study groups. In this sense, we aim to address different aspects of former criticism with our study design and to enhance knowledge about OLP effects.

To sum up, a positive OLP response in PMS would form the basis for future studies investing how to successfully harness placebo effects, in an ethical fashion, in clinical practice and to optimise PMS interventions that often entail side-effects.
